#### Secondary outcomes

There will be two secondary outcomes. The first is cervical cancer knowledge. Women in Groups 2 and 3 receive a 1-hour health education session. Thus, changes in cervical cancer knowledge from baseline to follow-up will be compared across the three groups. For each woman, the change in proportion of questions answered correctly will be examined.

The other secondary outcome will be access to care. Although improving access to care is not specifically part of the intervention, conceptually, a major role for CHWs is linking women in their communities to health care. Thus, as a secondary outcome we will determine the impact of our CHW intervention at improving access to healthcare. This will include an analysis of survey questions regarding having health insurance, a usual source of preventive care, and number of visits to a provider within the last year. By including this as a secondary outcome, it will help us examine whether access to care improved among participants having a CHW. This data will also help to address concerns that women in Group 3 who receive negative results from their completed HPV may believe that they are healthy and do not need to see a health care provider. That is, it will allow us to examine whether access among participants in Group 3 remained the same as those in Group 2.

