**Design:**

The South Florida Center for the Reduction of Cancer Health Disparities (SUCCESS) is conducting a three-arm randomized trial among Hispanic, Haitian, and African American women in Miami-Dade County. Community health workers (CHW) based in each of three communities are recruiting 200 women at each site (600 total). Eligibility criteria include women aged 30–65 years who have not had a Pap smear test in the last 3 years. Prior to randomization, all women undergo a standardized structured interview. Women randomized to public health outreach, Group 1, receive culturally tailored educational materials. Women in Group 2 receive an individualized comprehensive cervical cancer CHW-led education session followed by patient navigation to obtain the Pap smear test at community-based facilities. Women in Group 3 have the option of navigation to a Pap smear test or performing HPV self-sampling. The primary outcome is self-report of completed screening through a Pap smear test or HPV self-sampling within 6 months after enrollment.

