#### Intervention Group 3: HPV self-sampling option

Women randomized to this arm receive the same health education session as Group 2. In addition, the education includes information on HPV self-sampling as an alternative screening method. They receive an offer of choosing between the HPV screening at the conclusion of the educational session or navigation services to a traditional Pap smear test at a local healthcare facility. If the woman chooses the HPV self-sampling strategy, the CHW provides detailed instructions to complete the sample collection. Using standardized operating procedures and study-specific visual aids and flipcharts we developed, they teach women the proper self-sampling collection technique. Women complete the test in a bathroom while the CHWs wait outside to answer any questions that may arise during the process.

We are using the HPV self-sampling device developed by Preventive Oncology International and the National Institutes of Health, which is a nylon swab 2 cm in diameter and 15 cm in length. Based on prior feedback on comfort and ease of use from earlier study participants, we are using the sampler without the outer sheath. After the woman collects the sample using the swab, she removes the swab out of her vagina and gives it to the CHW. The CHW puts the swab in a pre-labeled liquid media vial (ThinPrep, Holigic Inc., Bedford, MA, US) stirs the sample, caps the bottle, and stores the sample in a re-sealable plastic bag in a locked cabinet. Once a week, the CHW delivers the samples to the University of Miami’s Department of Pathology for processing. The sample is then sent to an outside CLIA approved laboratory (Quest Diagnostics Inc.) for HPV testing. Initially our specimens were being processed by Quest using the Cervista HPV Invader Assay (Holigic In.) [24]. This was later changed to APTIMA HPV Assay (GenProbe Inc.). The former tests for HPV using a DNA based two-step signal amplification method and the latter tests for mRNA using a three step transcription-mediated amplification assay [25]. Both assays test for the 14 HPV strains which have been identified as high risk HPV by the International Agency for Research on Cancer [26] (i.e., 16, 18, 31, 33, 35, 39, 45, 51, 52, 56, 58, 59, 66, 68). They have similar sensitivities for detection of cervical intra-epithelial neoplasia (CIN2+) [27].

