After the specimen is collected, the CHW asks the woman a few additional questions concerning her experience with the procedure, including ease of use, perceived correctness of device use, degree of pain associated with use, and willingness to recommend the device to family or friends as an alternative to Pap smear testing. The CHW also stresses the importance of seeing a health care provider to address any other health issues she identified during their conversations. The CHW also advises the woman that a positive result (i.e., positive for HPV high risk), will require follow-up up to ensure she receives recommended medical care. In rare cases where a submitted sample is deemed as quantity not sufficient by the laboratory, CHW will ask the woman to undergo a second HPV sampling.

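### The provider-visit item does not set aside the clinic Pap visit, so a Group 3 versus Group 2 difference in visits cannot by itself show false reassurance

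*Protocol article*

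**What the plan says.** Under Secondary outcomes, access to care is assessed from survey questions on "having health insurance, a usual source of preventive care, and number of visits to a provider within the last year". One stated use is to address the concern that Group 3 women with a negative HPV result "may believe that they are healthy and do not need to see a health care provider". The section says of these data that "it will allow us to examine whether access among participants in Group 3 remained the same as those in Group 2".

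The two arms reach screening by different routes. The abstract's Design paragraph gives Group 2 an education session and then "patient navigation to obtain the Pap smear test at community-based facilities". The section on Intervention Group 3 describes "choosing between the HPV screening at the conclusion of the educational session or navigation services to a traditional Pap smear test". For those who take the first option, "Women complete the test in a bathroom while the CHWs wait outside". No facility visit is involved.

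The article neither says that the Pap visit counts as a provider visit nor excludes it.

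**The concern.** A Pap test at a health facility is a visit to a provider. A Group 2 woman who is screened through the study makes such a visit; a Group 3 woman who self-samples can be screened without one. If women in the two arms sought all other care at the same rate, their visit counts could still differ because the test was done in different places.

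The question in Secondary outcomes is whether a negative HPV result makes women stop seeing providers. Fewer visits in Group 3 could be read as that effect when it reflects only the missing Pap visit. If few women self-sample, the extra Pap visits in Group 3 could instead hide a real fall in other care. At stake is the reading of one item of one secondary outcome; the primary result is untouched.

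**Working it through.** The article gives no figure for the access outcome, so there is none to reproduce. The calculation below sizes the part of the visit difference that comes from the Pap visit alone.

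**Inputs from the article.** Group 2 is planned at 20 points above Group 1, and Group 3 at 15 points above Group 2 (Sample size). Total enrolment is 600, attrition is considered from 0% to 30% (Sample size), and a Bonferroni correction applies to secondary outcomes (Statistical analysis).

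**Assumptions, not in the article.** Group 1 screening rate b = 0.20 to 0.40. Share of screened Group 3 women who self-sample s = 0.5 to 0.8, with lower values shown for direction. SD of the visit count 2 to 3. Equal allocation, 200 per arm. Non-screening visits equal in both arms.

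**Step 1. Pap visits per woman.**
- Group 2: b + 0.20
- Group 3: (b + 0.35)(1 − s)
- Difference, Group 2 minus Group 3: d = (b + 0.20) − (b + 0.35)(1 − s)

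| b | s = 0 | s = 0.3 | s = 0.5 | s = 0.8 | d = 0 at s = |
|---|---|---|---|---|---|
| 0.20 | −0.15 | 0.015 | 0.125 | 0.29 | 0.27 |
| 0.30 | −0.15 | 0.045 | 0.175 | 0.37 | 0.23 |
| 0.40 | −0.15 | 0.075 | 0.225 | 0.45 | 0.20 |

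The last column is 0.15/(b + 0.35). For s between 0.5 and 0.8, d runs from 0.40 − 0.55 × 0.5 = 0.125 to 0.60 − 0.75 × 0.2 = 0.45 visits per woman.

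**Step 2. What a test would do with it.** Two secondary outcomes give α = 0.05/2 = 0.025, so z = 2.241. With SE = SD × √(2/n), the two-sided rejection probability is Φ(d/SE − z) + Φ(−d/SE − z).
- n = 200 per arm: SE = 0.20 (SD 2) or 0.30 (SD 3). Smallest case 0.125/0.30 = 0.42, about 4%. Largest case 0.45/0.20 = 2.25, about 50%.
- n = 140 per arm (200 × 0.7): SE = 0.239 or 0.359. Smallest case 0.35, about 3%. Largest case 1.88, about 36%.

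The chance of a significant difference when other care is identical is therefore about 3% to 50%, against 2.5% by design.

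**Step 3. Recall window.** The item covers a year and follow-up is at six months. The window therefore takes in the whole period in which a study-prompted Pap occurs, and adds visits from before enrolment that randomisation balances on average. It does not remove d.

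**The case against.** The strongest reply is that the article only names survey questions. How a visit is worded and coded is detail that a full protocol or analysis plan may hold, and a rule excluding the screening visit could be there. That stands as a caution: the article does not state that the Pap visit is counted. But it does claim that these items will answer the Group 3 versus Group 2 question, and the visit item as worded does not separate the two explanations.

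A reader might go further and infer the following. The article does not support these readings.
- *The access outcome as a whole favours Group 2 by construction.* Only one of three items is mechanically affected. A Pap visit does not confer insurance, and could change a woman's regular place of care only indirectly. Only Group 2 women who complete a Pap gain the visit, and Group 3 women may choose a Pap too.
- *A self-sampled woman cannot register a visit.* She can make other visits: "The CHW also stresses the importance of seeing a health care provider to address any other health issues". Women with a positive result need medical follow-up, which offsets part of any deficit, although those are not the women whose reassurance is in question.
- *The comparison is biased.* The randomised difference in total visits is a valid effect of assignment. The difficulty is what it can be taken to mean.
- *The comparison of the CHW arms with Group 1 is inflated.* Secondary outcomes gives linkage to health care as a major CHW role. A navigated clinic visit is that linkage, so counting it there fits the stated purpose.
- *The chance of a spurious finding reaches 61%.* That is the same extreme corner (2.25 standard errors) tested at an uncorrected 5% with no attrition, and the article plans a Bonferroni correction.

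**Conclusion.** The point holds for the visit item and for the Group 3 versus Group 2 false-reassurance question. A Group 3 deficit in provider visits would not by itself show that women with negative HPV results withdrew from care, and equality would not by itself rule it out.

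The Pap-visit component is 0.125 to 0.45 visits per woman in Group 2's favour under the assumptions above. It is zero at a self-sampling share of about 20% to 27%, and is 0.15 in Group 3's favour if nobody self-samples. Only the increments of 20 and 15 points come from the article; the Group 1 rate, the self-sampling share and the SD are assumed, so neither size nor sign can be fixed from the document. This is a flaw of interpretation in one item of a secondary outcome.

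**What to change.** Report insurance, regular source of preventive care and provider visits as three separate results. Base the Group 3 versus Group 2 statement about false reassurance on provider visits other than the cervical screening visit and its direct follow-up. Derive this by subtracting one visit for each reported clinic Pap since enrolment, by the same rule for every woman in every arm. Report total visits alongside, and keep total visits for comparing the CHW arms with Group 1.

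The cost is one derived variable from answers already collected, provided the interview recorded whether the test was a Pap or a self-sample. Trial status reports 582 of 600 women enrolled, so a derivation applied to all women is preferable to a reworded question that would leave two versions of the item.

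The downside is small but must be stated. The subtraction removes too much when the Pap was done at a visit made for another reason, or when a Pap is reported that did not take place. The Discussion cites over-reporting of nearly 30 percentage points, while noting that those studies concerned women asked for the first time. Such errors would fall most heavily on the arm with more Pap reports, which is why both versions should be shown.

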#### Sample size

In the study, we are recruiting 600 women from three study sites. The sample size was chosen to detect effects associated with a 20 point increase in the proportion of women screened in Group 2 (CHW) versus Group 1 (outreach) and an additional 15 percentage point increase in Group 3 (HPV self-sampling) versus Group 2. In addition, as women are randomized within each site, sample size calculations were adjusted to account for clustering of patients within each community. Based on these parameters, we examined power estimates under a variety of assumptions for attrition with estimates ranging from 0% to 30%. As shown in Figure 1, with a total sample size of 600 women (200 women in community), we will have sufficient power for the main study hypotheses, under a variety of attrition rate assumptions at a 0.05 level of significance.

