**Figure 1 Fig1:**
[figure not shown]
**SUCCESS sample size.** Legend: Figure shows the sample size needed (Y axis) to achieve statistical significance with 80% and 90% power, based on varying estimates of attrition (X axis).

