#### Allocation and blinding

Once women complete the intake questionnaire they are randomized into one of three possible interventions by the study coordinator who has the pre-generated randomization list from the study statistician. As the study design is hierarchical, with each participant nested within a site, the randomization is based at the site level. A study coordinator notifies the CHW assigned to that woman of the group assignment, and the CHW then follows-up with the women within a week, informing them of their assignment. If women are randomized to Groups 2 or 3, a follow-up visit is scheduled, ideally no later than a month from randomization. The RA who conducts the initial intake visit and 6-month follow-up assessment is blinded to study allocation. However, both women and CHWs are aware of the group to which each participant was randomized.

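### Randomising women within each site makes site a stratum, so it is no reason to adjust the sample size for clustering; the power basis and the allocation wording need restating

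*Protocol article*

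**What the plan says.** The Sample size section of the protocol article sets out two contrasts. It states that "The sample size was chosen to detect effects associated with a 20 point increase in the proportion of women screened" between Groups 1 and 2, and "an additional 15 percentage point increase in Group 3 (HPV self-sampling) versus Group 2". The total is 600 women, 200 from each of three communities, tested "at a 0.05 level of significance". The clustering statement is: "as women are randomized within each site, sample size calculations were adjusted to account for clustering of patients within each community". Power is called sufficient for attrition between 0% and 30%. The legend of Figure 1 reads: "Figure shows the sample size needed (Y axis) to achieve statistical significance with 80% and 90% power", plotted against attrition. The figure itself is not available here.

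The Allocation and blinding section says: "As the study design is hierarchical, with each participant nested within a site, the randomization is based at the site level". The same paragraph has the study coordinator assigning each woman, after intake, to one of three interventions from a pre-generated list. The section on the CHWs says that the three study CHWs assist participants in all three arms, and the Discussion says that there is one CHW per community.

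The Statistical analysis section compares the arms by chi-square tests and explores covariates by logistic regression. It does not say how site enters the primary comparison. Differences in effect between communities are left to the subgroup analysis, which is labelled hypothesis-generating.

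**The concern.** A clustering adjustment is needed when whole groups are allocated to one arm, because the differences between groups then become part of the treatment contrast. Here each community supplies women to all three arms. A community with a high screening rate raises all three arms alike, and the difference between arms is unaffected. Within-site randomisation is therefore the reason not to inflate, yet it is given as the reason for adjusting.

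Two things are at stake. First, the statement of sufficient power rests on an adjustment whose stated rationale does not fit the design, so a reader cannot tell what power the trial has for each contrast. Second, the documents describe site in three ways that do not fit together: as a cluster in the sample size, as the level of randomisation in the allocation section, and not at all in the comparison of arms. The correct role, a stratum, is stated nowhere.

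**Working it through.** **Inputs from the protocol article.** 600 women in three communities of 200; differences of 20 points (Group 2 v 1) and 15 points (Group 3 v 2); level 0.05; attrition 0–30%.

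**Assumptions, because the article gives no figure.** Equal allocation (600/3 = 200 per arm); two-sided test; Group 1 rate p1 from 5% to 40%, with 50% and 60% also tried; p2 = p1 + 0.20; p3 = p2 + 0.15.

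**Can 600 be reproduced?** Not uniquely, since neither the Group 1 rate nor the size of the adjustment is stated.

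**Step 1. Requirement without inflation, 15-point contrast.**
n per arm = [1.960·√(2p̄(1−p̄)) + z_power·√(p2(1−p2) + p3(1−p3))]² / 0.15², where p̄ is the mean of p2 and p3.
Example, p1 = 20%, so p2 = 40% and p3 = 55%: [1.960·√0.49875 + 0.842·√0.4875]² / 0.0225 = (1.384 + 0.588)² / 0.0225, giving 173.
Over p1 = 5–40% the need is 152–173 per arm for 80% power (total 456–519). For 90% power the total is 609–693. So 600 lies above the uninflated 80% totals and just below the lowest uninflated 90% total.

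**Step 2. Power with 200 per arm, no inflation, no attrition.**
Power = Φ{[0.15·√n − 1.960·√(2p̄(1−p̄))] / √(p2(1−p2) + p3(1−p3))}.
Example, p1 = 20%: Φ[(2.121 − 1.384)/0.698] = 0.854.
Over p1 = 5–40%: 0.85–0.90 for the 15-point contrast, and 0.98 or more for the 20-point contrast.

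**Step 3. How much inflation 600 could bear.** Largest design effect at 80% power, 15-point contrast = 200/n: 200/173 = 1.16 to 200/152 = 1.32. If the usual form DE = 1 + (m − 1)·ICC was used, the largest ICC is:

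| Cluster size m | Largest ICC for 80% power |
|---|---|
| 67 (one arm in one site) | 0.16/66 to 0.32/66, about 0.0024–0.0048 |
| 200 (whole site) | 0.16/199 to 0.32/199, about 0.0008–0.0016 |

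For illustration at ICC 0.01 and p1 = 10–40%, power is 0.65–0.70 with m = 67 (DE 1.66) and 0.41–0.46 with m = 200 (DE 2.99). The 20-point contrast bears a design effect of 2.06–4.08 over p1 = 5–40%. At p1 = 50% and 60% the 15-point contrast bears 1.65 and 2.63.

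**Step 4. Attrition without inflation.** At 30%, 200 × 0.70 = 140 per arm. With p1 = 20%: Φ[(0.15·√140 − 1.384)/0.698] = 0.71. Over p1 = 5–40%: 0.71–0.77. In this range of p1 no design effect of 1 or more gives 80%. The protocol in fact counts lost women as not screened. If the planned rates apply to women who are followed up, the 15-point difference shrinks to 0.70 × 15 = 10.5 points with 200 still in each arm, and power is 0.56–0.67 for p1 = 10–40%. If the planned rates already count losses as unscreened, attrition takes nothing further.

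**Step 5. Does site variation harm this design?** Individual randomisation within three sites was simulated with a site-stratified test. Type I error was 0.047–0.051 for site ICCs (logit scale) from 0 to 0.16. Power for 40% v 55% was 0.86 with no site effect, 0.84 at ICC 0.05 and 0.81 at ICC 0.16. A cluster design effect at ICC 0.05 would imply about 0.30 (m = 67) or 0.14 (m = 200). So the cluster formula does not describe how this trial behaves. In two simulated settings with widely differing site rates, replacing an unstratified test by a stratified one raised power from 0.81 to 0.83 and from 0.72 to 0.78. Stratifying never lost power.

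**The case against.** The article states no formula. An adjustment for clustering need not be an inflation by a cluster-trial design effect; it could be a multisite calculation that hardly changes the total. The inputs may stand in the full protocol or in Figure 1, and leaving them out of an article is no fault. This stands, and it rules out any claim that a printed number is wrong.

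Any such error would be conservative for the design actually used, and the Trial status section reports 582 of 600 enrolled. This also stands: nothing here argues for a different sample size.

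The allocation sentence may be only loose wording, since the same paragraph describes individual assignment. That is the likely meaning. A reader might infer from the sentence that whole communities were allocated to arms, but the Overview and trial design section and the rest of that paragraph exclude it. The wording is still wrong for the design.

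With one CHW per community, the effect of an arm may vary between sites. That is possible, but it is an arm-by-site interaction. It is not the reason that the Sample size section gives, and a design effect for correlated outcomes within a site does not address it.

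The logistic models may include site among their covariates. The article does not say so, and the chi-square comparison of arms does not use it.

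**Conclusion.** The point holds as a fault in the stated rationale and in the description of the design. Randomising individuals to all arms within each site does not support inflating for clustering by community, the allocation sentence misdescribes the same design, and the stated comparison of arms leaves site out.

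A reader might go further and infer that 600 women are too few once the adjustment is applied. The documents do not support that. The ICC, the design effect and the Group 1 rate are unknown. A near-zero ICC, or a Group 1 rate of 50% or more at moderate ICCs, can keep 80% power, and the 20-point contrast bears much more inflation than the 15-point one. Nor does the misplaced rationale leave the trial underpowered: without inflation or attrition the 15-point contrast has 85–90% power.

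What can be said is conditional on 200 per arm, a two-sided 0.05 test and Group 1 rates of 5–40%. Any inflation compatible with 80% power for the 15-point contrast is at most about 1.16–1.32. At the upper end of the stated attrition range, power is 71–77% with no inflation at all. Under those assumptions, the statement of sufficient power across the attrition range is not met at 80% for that contrast.

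**What to change.** 1. In the Sample size section, remove the clustering rationale, or replace it with the adjustment that was actually made and its size.
2. Restate power for each contrast across 0–30% attrition, for an individually randomised trial stratified by site. Give the assumed Group 1 rate, and say whether the planned rates already count lost women as unscreened. Bring Figure 1 into line with this basis.
3. In the Allocation and blinding section, reword the sentence to: *women are individually randomised, with allocation stratified by site*.
4. In the Statistical analysis section, include site in the primary arm comparisons as a stratum or fixed effect, by a stratified test or by logistic regression with site. Leave variation of the arm effect between communities to the planned subgroup analysis.

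The cost is one recalculation, two reworded sentences and one added term in the analysis. The sample size stays at 600, and enrolment and conduct do not change. Because the primary outcome is examined every 6 months, the analysis change should be dated and justified by the design before the final comparison is run.
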